In pediatric patients, a higher number of attempted punctures during a single LP procedure is associated with a doubled risk of TLP [15]. However, one cannot presume constant success at the first attempt. In pediatric patients with ALL, the mean first puncture success rate of LP with a single skin penetration is good to excellent varying from 70% up to 95% [16–19]. In adults with leukemia, high success at the first attempt is associated with a roughly halved incidence of TLP [20], whereas in pediatric patients with ALL, the probability of TLP was about fourfold if the first attempt was not successful [19]. High success at the first attempt likely contributes also to a low incidence of post-dural puncture headache (PDPH) [17], which is the most considerable adverse event after an LP procedure. In children with ALL, however, the incidence of PDPH is yet relatively low varying around 10% [15–19].

Experience and training contribute to an improved performance in LP [17, 18]. The success of the LP procedure can also be improved by image guidance either before inserting the spinal needle into the body or in real-time during the procedure. According to recent meta-analyses [21–23], ultrasound guidance is associated with a halved incidence of TLPs, an improved success rate of LP procedures, and a reduced incidence of failed procedures compared to the traditional palpation-based procedures. Particularly patients with high body mass index (BMI), anatomic abnormalities, young age, or a history of many failed attempts may be referred to ultrasound imaging before or during the LP procedure [21, 24].

While the evidence for the clinical utility of ultrasound imaging in performing LP is convincing [21–23], the true real-time ultrasound guidance requires a physician’s one hand to use the ultrasonic probe and the other to advance the spinal needle, let alone the need for bedside imaging equipment, and provider’s adequate proficiency to employ ultrasound imaging and interpret the images in real-time. These requirements may modify the standard provision of LP the physicians who are accustomed to performing. Thus, a needle guidance method not requiring specific expertise and simultaneous operation of the imaging equipment but still providing real-time feedback on the needle tip location would be a valuable option.

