Recently, clinical studies of adults [25], neonates and infants [26], and pediatric patients with ALL [19] showed the feasibility and safety of a novel bioimpedance-based spinal needle system in LP procedures. This system, called the IQ-Tip system, measures bioimpedance at the tip of the spinal needle with 15 different frequencies and classifies the bioimpedance data 200 times in a second. This means that the tissue classification is virtually real-time (performed at every 5th ms) and the spatial sensitivity is high (~ 1 mm^3^). The system gives an audio-visual alarm when the needle tip reaches CSF in the subarachnoid space and indicates the correct location for CSF sampling or administration of intrathecal therapy. In our recent single-arm study of pediatric patients with ALL, the first attempt was successful in 80% of procedures, and the incidence of TLP was 17%. Further, neither the success rate nor the incidence of TLP was associated with the provider’s experience or the patient’s overweight [19].

Given the promising real-world clinical experience, we hypothesize that the performance of the IQ-Tip system is at least comparable to the conventional spinal needle regarding the incidence of TLP in LP procedures of pediatric hemato-oncology patients. The primary objective of the present trial is to demonstrate that the observed incidence of TLP with the IQ-Tip system will indicate either noninferiority or not only noninferiority but also superiority compared to the conventional spinal needle, which is the current standard clinical method. The secondary objectives are to compare the first puncture success rate and the incidence of complications, particularly the incidence of PDPH, in the LP procedures performed with the IQ-Tip system and conventional spinal needle. No formal hypotheses are set for the secondary outcomes.

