#### The LP procedure A

Study procedure A will be performed with the IQ-Tip system (Injeq Plc, Tampere, Finland), which is a CE-marked medical device as per Medical Device Regulations (MDR EU 2017/745) approved for any clinically indicated LP procedure. The system comprises either a 40-mm, 65-mm, or 90-mm-long 22G Quincke-type spinal needle (IQ-Tip spinal needle), a bioimpedance analyzer, and a thin, flexible coaxial cable for connecting the needle to the analyzer. The IQ-Tip spinal needle is identical to the conventional Quincke-type 22G spinal needle with a stylet, except the stylet is configured as a bioimpedance electrode and it has a cable connector at the handle end. The analyzer has an internal memory, where the raw bioimpedance data collected at a 200-Hz sampling rate will be stored for further post-hoc analysis.

Performing the LP procedure with the bioimpedance needle is basically like that with the conventional spinal needle. Also, the removal and reinsertion of the stylet do not differ from the conventional spinal needle. Only the cable at the handle end is the major difference.

When performing the LP procedure with the IQ-Tip system and perceiving the CSF detection alarm, the provider can either remove the stylet and check for CSF flow through the needle or continue the puncture upon clinical judgment on the location of the needle tip. Similarly, irrespective of the alarm, the provider can remove the stylet and check for CSF flow whenever considered necessary.

When the needle tip is correctly in the subarachnoid space verified by CSF flow, the provider will take the CSF sample and deliver the intrathecal therapy according to the patient’s treatment protocol.

Right after performing the study LP procedure with the IQ-Tip system, the provider will evaluate the performance and record the results concerning a successful procedure at the first attempt, number of attempts needed for a successful procedure, number of stylet removals in the successful procedure, failure to perform the procedure, and the accuracy of perceived alarms on the patient’s CRF. Also, patients’ immediate complications and device deficiencies, if any, will be recorded on CRF.

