#### The LP procedure B

Study LP procedure B will be performed with a conventional 22G Quincke-type spinal needle according to the standard clinical practices of the investigational sites.

When performing the LP procedure with the conventional needle, the provider can, upon clinical judgment on the location of the needle tip, remove the stylet and check for CSF flow through the needle, or continue the puncture.

When the needle tip is correctly in the subarachnoid space verified by CSF flow, the provider will take the CSF sample and deliver the intrathecal therapy according to the patient’s treatment protocol.

Right after performing the study LP procedure with the conventional needle, the provider will evaluate the performance and record the results concerning successful procedure at the first attempt, total number of attempts needed for a successful procedure, number of stylet removals in the successful procedure, and failure to perform the procedure on the patient’s CRF. Also, patients’ immediate complications and device deficiencies, if any, will be recorded on CRF.

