The number of attempts needed for a successful LP procedure will be recorded for each study procedure. Congruent with the definition of the first puncture success rate, an attempt denotes any new penetration of the skin. Being successful means that, irrespective of the number of attempts, a CSF sample is eventually obtained and/or the intrathecal therapy is performed as appropriate for the given procedure. The number of failed LP procedures will be registered as well. An LP procedure is considered failed if the physician(s), even after multiple attempts, conclude that the subarachnoid space cannot be verifiably reached, and the procedure remains incomplete with the available personnel or equipment due to any reason. Also, the provider’s decision to use other than the assigned spinal needle due to any reason is considered a failed procedure. These procedural outcomes will be reported for both arms.

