**Fig. 2 Fig2:**
[figure not shown]
Schematic on the relation between the numbers of traumatic LP procedures (TLP) with the IQ-Tip system and conventional spinal needle required to indicate noninferiority (green area) or not (red area)

The primary statistical comparison of outcome variables will be based on the true use of the allocated spinal needles in the study LP procedures. Therefore, per-protocol analysis will be employed in the efficacy analysis as recommended for noninferiority trials [32]. The incidences of TLP and PDPH as well as the first puncture success rate between the respective study arms will be compared with the Chi-squared test. The 95% confidence intervals (95% CI) for the difference will be calculated using the exact Clopper-Pearson method. Between-arm comparisons of blood and CSF data, other performance parameters, and incidences of other complications will be performed for descriptive purposes. Definitions of the outcome variables to be used in the efficacy analysis are presented in Table 2 in terms of domain, measurement, metric, aggregation, and time point according to a recommended framework for clinical trials [33, 34]. In case of missing data, data estimation nor imputation will not be performed.

**Table 2 Tab2:** Definitions of the outcome variables (only those domains pertinent to the efficacy analysis are presented) in terms of domain, measurement, metric, aggregation, and time point

Domain	Specific measurement	Metric	Method of aggregation	Time point
Incidence of TLP	Flow cytometry	Erythrocyte count ≥ 10/µL (yes/no)	Proportion	Each study LP procedure
First puncture success rate	Provider’s self-report on CRF	Occurrence (yes/no)	Proportion	Each study LP procedure
Incidence of PDPH	Symptom diary	Occurrence (yes/no)	Proportion	Within 1 week after each study LP procedure
Peripheral blood analysis	Flow cytometry	Erythrocyte count (cells/µL) Hematocrit (%) Hemoglobin (g/L) Leukocyte count (cells/µL) Thrombocyte count (cells/µL) Existence of blasts (yes/no)	Mean Mean Mean Mean Mean Proportion	Each study LP procedure
CSF analysis	Flow cytometry	Erythrocyte count (cells/µL) Leukocyte count (cells/µL) Existence of blasts (yes/no)	Cumulative distribution curve Mean Proportion	Each study LP procedure
Number of LP attempts	Provider’s self-report on CRF	Number	Median	Each study LP procedure
Number of failed procedures	Provider’s self-report on CRF	Occurrence (yes/no)	Proportion	Each study LP procedure

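### Table 2 summarises the number of LP attempts by a median that will be 1 in both arms, and punctures made in failed procedures have no defined count

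*Protocol article*

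**What the plan says.** Under Other outcomes, the protocol article states: "The number of attempts needed for a successful LP procedure will be recorded for each study procedure". The same paragraph fixes the unit: "an attempt denotes any new penetration of the skin". A procedure completed with a single skin puncture therefore scores 1.

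The procedure sections use the same success-based definition. For arm A the provider records "number of attempts needed for a successful procedure, number of stylet removals in the successful procedure, failure to perform the procedure". For arm B it is the "total number of attempts needed for a successful procedure".

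In Table 2 (Data analysis) the row reads "Number of LP attempts Provider’s self-report on CRF Number Median". The last entry is the method of aggregation, and no other statistic is named for this outcome.

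The expected level of success is in the Background. For the IQ-Tip system, "the first attempt was successful in 80% of procedures". For pediatric ALL in general, "the mean first puncture success rate of LP with a single skin penetration is good to excellent varying from 70% up to 95" per cent.

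Failed procedures have their own definition under Other outcomes and their own Table 2 row, reported as a proportion. The definition covers procedures abandoned after several attempts and any decision to use a needle other than the assigned one.

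**The concern.** A median equals 1 whenever more than half of the values are 1. If 70% to 95% of procedures succeed at the first puncture, the result for this outcome is known before any data are collected: 1 in arm A and 1 in arm B. First puncture success already separates one puncture from more than one. What the attempts outcome can add is the spread among the remaining procedures (two punctures or five), and the median discards exactly that.

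The definition raises a second, smaller problem. A procedure that never succeeds has no number of attempts needed for success, yet the text asks for a value for each study procedure. Failed procedures may include some with many punctures, and those punctures have no defined place in the count.

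The Background gives the outcome some relevance: it reports that more attempts in one procedure are associated with a doubled risk of traumatic LP, the event behind the primary outcome.

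**Working it through.** **Inputs from the protocol article**
- First puncture success: 80% with IQ-Tip; 70% to 95% in pediatric ALL (Background). The range is taken to cover arm B.
- Aggregation of attempts: median (Table 2).
- About 150 procedures per arm (Data analysis).

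**Planned number per arm.** The article gives no figure for attempts, so the stated sample size only sets n for the check. With traumatic LP at 20% versus 30%, a 5-point margin and 90% power, n = (z₁₋α + z₀.₉₀)² × (0.7×0.3 + 0.8×0.2) / (0.10 + 0.05)².
- One-sided α = 0.05: 141 per arm; power at 150 is 91.5%. This agrees with the stated figure of about 150 at 90%.
- One-sided α = 0.025: 173 per arm; power at 150 is 85.5%.

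n = 150 is used below.

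**Is the median 1?** With n = 150, the median is 1 if at least 76 procedures score 1. Treating procedures as independent, P(median = 1) = P(X ≥ 76), with X binomial(150, p):

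| Share scoring 1 (p) | P(median = 1) |
|---|---|
| 0.60 | 0.992 |
| 0.70 | above 0.999999 |
| 0.80 | 1.0000 |
| 0.95 | 1.0000 |

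First puncture success also requires that the primary provider does not change, so the share of procedures with one penetration is at least as high as the success rate. Using that rate for p is therefore conservative.

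**Can the medians differ between arms?** In 20,000 simulated trials with geometric attempt counts (an assumption), the two medians differed in 0 runs for 80% versus 70% and in 0 runs for 95% versus 70%. The means do separate: 1/0.80 = 1.25 versus 1/0.70 = 1.43, and 1/0.95 = 1.05 versus 1.43.

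**What the median hides.** Two hypothetical arms, each with 80% first puncture success:
- 20% need 2 attempts: mean = 0.8×1 + 0.2×2 = 1.2.
- 20% need 5 attempts: mean = 0.8×1 + 0.2×5 = 1.8.

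First puncture success (80%), the median (1) and the upper quartile of the distribution (1) are the same in both. In a sample of 150 at 80% success, the upper quartile is 1 with probability about 0.93, so adding the interquartile range would usually not help.

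**Effect of leaving failures out.** With an assumed 5% failure rate, the share scoring 1 rises from 0.80 to 0.80/0.95 = 0.84, or from 0.70 to 0.70/0.95 = 0.74. The median is 1 either way. The mean can move: if 80% succeed at attempt 1, 10% at attempt 2 and 10% fail after 4 attempts (assumed figures), it is (0.8 + 0.2)/0.9 = 1.11 among successes and 0.8 + 0.2 + 0.4 = 1.40 over all procedures.

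**The case against.** The case on the other side is strong on consequence.

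- **Other statistics are allowed.** The Data analysis section opens with a general list (mean, SD, median, interquartile range, range, proportions) to be used where they suit the data. Mean, SD and range would all separate the two arms in the example above. This stands: it would be too much to infer that the trial cannot show a difference in attempts. But the list is generic, and Table 2, which assigns a statistic to each outcome, names only the median here.
- **First puncture success carries the main contrast.** It is a secondary outcome with all procedures in the denominator, compared by a chi-squared test with a confidence interval. A needle that more often needs a second puncture will be seen there. This stands, and it confines the loss to the spread beyond the first attempt. No passage suggests that the arms will differ in that spread.
- **Failures are not lost.** A reader might infer that failed procedures drop out of the trial's results. They do not: they are recorded on the CRF in both arms, reported by arm, and counted against first puncture success. Only the punctures made in them lack a defined value.
- **The CRF is not shown.** It may already capture attempts in failed procedures, so the gap is established in the text and not on the form.
- **The link to traumatic LP is an association.** The Background does not present the number of attempts as the cause, and attempts are not a predictor in the exploratory logistic model.

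**Conclusion.** The point holds in a narrow form. At the protocol's own success rates, the summary that Table 2 names for attempts will be 1 in both arms (probability above 0.999999 per arm at 70% success and 150 procedures) and so conveys nothing beyond first puncture success. Separately, the count is undefined for failed procedures. The first part rests on first puncture success staying clearly above 50% in both arms; even at 60% the probability is 0.992. It does not depend on how failures are handled.

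The consequence is minor. This is a descriptive outcome with no hypothesis, and the primary analysis, the sample size and the tested secondary outcomes are unaffected. The documents do not support the stronger reading that the trial is blind to repeat punctures or ignores failures.

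**What to change.** 1. In Table 2, replace the median for number of LP attempts with the distribution by arm (1, 2, 3 or more), adding mean and range if wanted.
2. In The LP procedure A, The LP procedure B and Other outcomes, define the count as the total number of skin penetrations made with the assigned needle in every study LP procedure, failed ones included.
3. Keep failed procedures as their own row. Do not merge them with a category of 3 or more attempts: failure includes a change of needle for any reason, which need not follow many punctures, and the article gives no basis for 3 as a cut-off in a composite.

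Cost: the Table 2 change uses data already collected. The definition needs a small edit to the text, and to the CRF only if the form does not already capture punctures in failed procedures. The first study procedure was on 11 May 2023, so the change goes through the amendment route described under Ethical and regulatory considerations. If the CRF does need changing, punctures in failures before the change may not be recoverable.

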#### Performance of the IQ-Tip system

For the study arm A only, the CSF detection sensitivity and false detection rate of the IQ-Tip system will be determined as performance outcomes using the data registered in the patient-specific CRFs. The total numbers of correct alarms (i.e., # of true positive (TP) detections when the CSF detection alarm occurs and CSF flows after the stylet removal), missing alarms (i.e., # of false-negative (FN) detections when the CSF detection alarm do not occur, but CSF flows after the stylet removal), and false alarms (i.e., # of false-positive (FP) detection when the CSF detection alarm occurs but CSF does not flow after the stylet removal) will be recorded.

The CSF detection sensitivity is calculated using Eq. 4.4$$\mathrm{CSF\;detection\;sensitivity}=100\times \frac{\mathrm{Total\;number\;of\;TPs}}{\mathrm{Total\;number\;of\;LP\;procedures}}\mathrm{ \%}$$

The false detection rate is calculated using Eq. 5.5$$\mathrm{False\;detection\;rate}=100\times \frac{\mathrm{Total\;number\;of\;FPs}}{\mathrm{Total\;number\;of\;LP\;procedures}}\mathrm{ \%}$$

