#### Secondary outcomes

Secondary outcomes are the first puncture success rate and the incidence of PDPH related to the LP procedures in both study arms.

The success of performing the procedure at the first attempt is defined by the following conditions: only one skin penetration with the needle is done, an eligible CSF sample is obtained and sent for the laboratory analysis, and/or the intrathecal therapy is delivered, and the primary provider does not change during the procedure. Multiple needle redirections are allowed provided that the needle tip remains beneath the skin. Multiple stylet removals and reinsertions are also allowed.

The percentage proportions of the first puncture success rate will be separately calculated for both study arms using Eq. 2.2$$\mathrm{First\;puncture\;success\;rate}=100\times \frac{\mathrm{Total\;number\;of\;succesful\;procedures\;at\;the\;first\;attempt}}{\mathrm{Total\;number\;of\;all\;procedures}}\mathrm{\%}$$

After each study LP procedure, the local study nurse or investigator will give the patient or parents a diary to be filled for reporting perceived symptoms or complications during the day of the procedure and seven subsequent days. These symptoms and complications include PDPH, headache, nausea, backache, fever, leaking, or inflammation at the puncture site. Conforming to the standard definition, PDPH is a severe headache that worsens in sitting or standing positions, eases after lying down, and occurs within 7 days after the procedure. After the week, the study nurse or investigator will contact the patient or parents and inquire about the diary data.

The incidence of PDPH will be separately calculated for both study arms using Eq. 3.$$\mathrm{Incidence\;of\;PDPH}=100\times \frac{\mathrm{Total\;number\;of\;procedures\;causing\;PDPH}}{\mathrm{Total\;number\;of\;all\;procedures}}\mathrm{\% }$$

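### Equation 4 divides correct alarms by all procedures and calls the result sensitivity, which holds only if each arm A procedure yields exactly one CSF-flow event; Equation 5 is a rate per procedure labelled as a percentage

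*Protocol article*

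**What the plan says.** The protocol article, section Performance of the IQ-Tip system, names two performance outcomes for arm A only and records three totals on the CRF:

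- TP: "correct alarms (i.e., # of true positive (TP) detections when the CSF detection alarm occurs and CSF flows after the stylet removal"
- FN: "missing alarms (i.e., # of false-negative (FN) detections when the CSF detection alarm do not occur, but CSF flows after the stylet removal"
- FP: "false alarms (i.e., # of false-positive (FP) detection when the CSF detection alarm occurs but CSF does not flow after the stylet removal"

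It then says "The CSF detection sensitivity is calculated using Eq" 4, which is 100 × TP divided by the total number of LP procedures. Equation 5, the false detection rate, is 100 × FP over the same denominator. Both carry a % sign. FN appears in neither equation.

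Three other places bear on the denominator. The LP procedure A section says that "irrespective of the alarm, the provider can remove the stylet and check for CSF flow whenever considered necessary". The Secondary outcomes section, defining first puncture success, adds: "Multiple stylet removals and reinsertions are also allowed". The Other outcomes section recognises failed procedures, in which the physicians "conclude that the subarachnoid space cannot be verifiably reached, and the procedure remains incomplete"; switching to a needle other than the assigned one also counts as failed.

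**The concern.** Sensitivity is the share of true events that the detector picked up. Under the section's own definitions a true event is CSF flow after stylet removal, with an alarm (TP) or without one (FN). The number of such events is TP + FN, not the number of procedures.

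Dividing by procedures mixes the detector's performance with the operator's success. A procedure in which the needle never reached CSF gave the device nothing to detect, yet it counts as a miss. Conversely, a missed alarm followed by a correct alarm in the same procedure counts as full detection, and the miss disappears.

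For Equation 5, FP is a count of alarms and one procedure can produce several. A figure in % will be read as a share of procedures or a share of alarms, and it is neither.

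These are the named performance outcomes of a study that the Discussion places within mandatory post-market follow-up. The Discussion also reports that some earlier users doubted the reliability of the alarms, which is the question these two figures answer.

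**Working it through.** The protocol gives no numerical value for either equation, so there is no figure to reproduce. The check is algebra plus an illustration.

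**Inputs.** N = 150 arm A procedures, from the sample size text in Data analysis. The TP, FN and FP definitions and both equations are from Performance of the IQ-Tip system. The counts of failed procedures, FN and FP are assumptions, shown as a range.

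**Equation 4, general relation.**

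TP/N = [TP/(TP + FN)] × [(TP + FN)/N]

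Equation 4 is therefore sensitivity multiplied by the mean number of CSF-flow events per procedure. It equals sensitivity when that mean is 1, falls below it when the mean is under 1, and exceeds it when the mean is over 1.

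**Downward case.** With at most one event per procedure, TP + FN = N − failed, so Equation 4 = sensitivity × (1 − failed share).

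| Failed (of 150) | FN | TP | Equation 4 | TP/(TP + FN) | Gap (points) |
|---|---|---|---|---|---|
| 0 | 15 | 135 | 90.0% | 90.0% | 0 |
| 3 (2%) | 0 | 147 | 98.0% | 100% | 2.0 |
| 3 (2%) | 15 | 132 | 88.0% | 89.8% | 1.8 |
| 8 (5.3%) | 0 | 142 | 94.7% | 100% | 5.3 |
| 8 (5.3%) | 15 | 127 | 84.7% | 89.4% | 4.7 |
| 15 (10%) | 0 | 135 | 90.0% | 100% | 10.0 |
| 15 (10%) | 15 | 120 | 80.0% | 88.9% | 8.9 |

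**Upward case.** Take 150 procedures: 130 with a TP only, 10 with an FN only, and 10 with an FN and then a TP. Then TP = 130 + 10 = 140 and FN = 10 + 10 = 20.

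- Equation 4: 140/150 = 93.3%
- TP/(TP + FN): 140/160 = 87.5%

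Equation 4 is 5.8 points too high.

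**Equation 5.**

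- 45 false alarms give 45/150 = 30.0%. That holds whether they fall one each in 45 procedures (30% of procedures affected) or three each in 15 procedures (10% affected).
- With 127 TP, the same 45 false alarms are 45/(127 + 45) = 26.2% of alarms.
- 180 false alarms give 180/150 = 120%. The value passes 100% only when false alarms average more than one per procedure, that is, more than 150 in 150 procedures.

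**The case against.** The strongest reply is that Equation 4 does take account of missed alarms through its denominator. Once CSF flow confirms the position, the LP procedure A section moves on to sampling and therapy, so a completed procedure will normally end in one TP or one FN. Then N = TP + FN and the two formulas are identical, as the first row of the table shows. This stands. A reader might infer from the absence of FN in the formula that missed alarms are simply ignored; that goes too far. The error is confined to procedures with no CSF-flow event or with more than one, and it is small if these are rare. If the performance analysis follows the per-protocol rule set for the primary comparison, procedures switched to another needle would also drop out, although the performance section does not say so.

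A second reply is that TP/(TP + FN) does not cure every counting problem. Two stylet removals in one procedure that both show CSF after an alarm add two TPs in either formula. That is also correct, and double-counted TPs are not an argument for one formula over the other.

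A third reply concerns Equation 5. A reader might infer that it is wrong because it can exceed 100%. The documents do not support that: the protocol calls it a rate, and false alarms per procedure is a clearly defined and legitimate rate. Nothing shows that the share of alarms that are false was the intended quantity. What remains is the % unit.

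Finally, neither measure is a primary or secondary outcome, and neither is listed in Table 2.

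**Conclusion.** The point holds in limited form. Equation 4 is not sensitivity under the protocol's own definitions unless every arm A procedure yields exactly one TP or FN, and the protocol foresees procedures that do not. Failed procedures alone make it too low by about 0 to 10 points over a failure share of 0 to 10%, with N = 150 and 0 to 15 FN. Procedures with both a missed and a correct alarm make it too high, so the error cannot be assumed to run against the device. All these sizes rest on assumed counts.

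Equation 5 needs a correct label, not a different definition. It would be tempting to conclude that both device-performance figures are wrong; only Equation 4 is, and only conditionally.

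The impact is minor. The sample size, the primary and secondary outcomes and the noninferiority conclusion do not depend on these descriptive arm A measures.

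**What to change.** - **Equation 4:** compute sensitivity as 100 × TP/(TP + FN). Report the number of arm A procedures without CSF flow separately.
- **Equation 5:** keep the ratio but label it false alarms per 100 procedures. Add the percentage of procedures with at least one false alarm, or report FP/(TP + FP) under its own name, the share of alarms that are false.

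The cost is one changed denominator, one changed label and one added line in the results. TP, FN and FP are already recorded for each procedure on the patient's CRF and failed procedures are already registered, so no new data are needed.
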